### Eligibility and recruitment

Consecutive patients referred to CR with IHD, ≥18 years of age, with a diagnosis of IHD (codes I20-I25), HADS score ≥ 8 on depression, anxiety or both, with access to a computer or smartphone, ability to use a computer or smartphone, and proficient in the Danish language are eligible for inclusion. Patients with severe psychiatric disorders (i.e., borderline disorder, schizophrenia or bipolar disorder), severe cognitive difficulties (e.g. severe brain damage, mental retardation, or dementia) that will prevent patients from participating, endorsement of suicidal ideation with daily suicidal thoughts (PHQ-9 item 9 > 2), participating in other intervention studies (unless they are clinical studies [e.g. medication trials]), or seeing a psychologist or mental health professional for the treatment of depression and anxiety, will be excluded (Fig. 1). Patients who were previously enrolled in the study and referred to CR due to a new cardiac event will not be eligible to participate a second time. Table 1 presents an overview of the recruitment procedure.

**Table 1 Tab1:** Overview of recruitment procedure

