## Sample size calculation

Based on Stauber et al. [34], a conservative estimate of the standard deviation of the mean of the HADS depression score at 3 months is 3.5. The minimal clinically important difference for the HADS is 2 points [35]. For a normal-based comparison of independent means, with a power of 90% (ß = 0.1) and a risk of Type 1 error of 5% (α = 0.05), the estimated required number of patients is *n* = 66 in each group. Considering a potential 30% dropout rate, the estimated number of needed participants is *n* = 94 patients in each group (n (total) = 188).

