## Patient-reported measures

Table 3 provides an overview of the patient-reported and related measures and their time of assessment used in *eMindYourHeart.* Standardised and validated questionnaires are supplemented with purpose-designed questions (e.g. to tap into patient satisfaction with CR).

**Table 3 Tab3:** Patient-reported outcome measures used and times of assessment

Construct assessed	Measure	Items	***Baseline***	***End of treatment***	***FU*** ***6 months***	***FU*** ***12 months***
Anxiety	Hospital Anxiety and Depression Scale (HADS-A)	7	X	X	X	X
Depressive symptoms	Hospital Anxiety and Depression Scale (HADS-D)	7	X	X	X	X
Anxiety symptoms	Cardiac Anxiety Questionnaire (CAQ-18)^1^	18	X	X	X	X
Depressive symptoms	Patient Health Questionnaire (PHQ-9)^1^	1	X	X	X	X
Loneliness	UCLA Loneliness Scale	3	X	X		
Social support	Multidimensional Scale of Perceived Social Support (MSPSS)	12	X			
Illness perceptions	Brief Illness Perceptions Questionnaire (B-IPQ)	9	X			
Quality of Life	HeartQoL	14	X	X	X	X
Perceived stress	Perceived Stress Scale	10	X	X	X	X
Health Anxiety and Somatic Complaints	Health Complaints Scale	24	X	X	X	X
Physical activity	Purpose-designed	2	X	X	X	X
Patient’s engagement in general CR	Purpose-designed	4		X		
Potentially negative effects of treatment	The Negative Effects Questionnaire (NEQ)^a^	20		X		
Cost-effectiveness/cost-utility^2^	EQ-5D-5L	6	X	X	X	X
Patient expectations to CR	The credibility/ expectancy questionnaire (CET)^a^	4	X			
Patient satisfaction with / evaluation of eHealth intervention	Internet evaluation and usability questionnaire^a^	6		X		
Patient satisfaction with CR	Purpose-designed measure	1		X		

*FU* Follow-up

^a^Questionnaire is only completed by patients in the intervention group [the CET is completed on the platform]

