## Statistical methods

Data will be analysed according to the modified intention-to-treat principle (i.e., all patients with a 3-month evaluation will be analysed as randomised). The intention-to-treat principle will be applied from the time that patients have initiated treatment (i.e., after the brief interview protocol that includes elements from the SCAN interview and motivational interviewing). Categorical variables will be summarised as n (%), continuous variables as min-max, mean (SD), and median. All summaries will be by randomisation group. The primary analysis will be a linear regression of depression scores at 3 months including randomisation group and strata as factors and baseline depression scores as covariate. Potential confounders, apart from baseline and stratification variables, identified by clinical consensus, will be included in multivariable analyses when appropriate (e.g. when performing sub-group analyses). A mixed effects model will be used to analyse the longitudinal change in HADS scores and HeartQoL scores, adjusting for strata, incorporating random effects to model the homogeneity within cluster and the correlation within patient across time. Pre-planned subgroup analyses will be conducted for the primary outcome with respect to: *(i)* type of IHD (stable versus unstable); *(ii)* sex (female versus male); *(iii)* age (median split); *(iv)* depression status at baseline (< 10 versus ≥11; *≥11 is considered a moderate score*). A sensitivity analysis will be conducted. The statistical analysis will be transparent, subject to review and approval by the project team.

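### The baseline-depression subgroups (< 10 versus ≥11) leave patients scoring exactly 10 in neither group; a minor error in one pre-planned subgroup analysis

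*Protocol article*

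**What the plan says.** The Statistical methods section introduces the subgroup work with "Pre-planned subgroup analyses will be conducted for the primary outcome with respect to", followed by four factors: type of heart disease, sex, age and baseline depression. The last is written as "depression status at baseline (< 10 versus ≥11", with the gloss that "≥11 is considered a moderate score".

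Under Eligibility and recruitment, patients enter with "HADS score ≥ 8 on depression, anxiety or both". Table 1 adds that the HADS must still be positive on the baseline questionnaire before randomisation. The table under Patient-reported measures lists "Hospital Anxiety and Depression Scale (HADS-D") with 7 items, measured at baseline and at every follow-up.

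The primary analysis in Statistical methods is a linear regression of the 3-month depression score on randomised group and strata, with the baseline depression score as covariate. The article does not restate the subgroup cut-points, name a third category or say where a score of 10 belongs.

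**The concern.** Two subgroups meant to compare lower with higher baseline depression should between them contain every analysed patient. The printed limits do not meet: the lower group stops below 10 and the upper group starts at 11. A patient with a score of 10 has no group.

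Two things follow if the rule is applied literally. First, the subgroup table will not add up to the analysed population, and the patients lost are those next to the cut-point. Second, an analyst who notices the gap must repair it during the analysis, although the purpose of pre-specifying a subgroup is to settle its definition beforehand.

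**Working it through.** **1. Which score is meant.** The subgroup line does not name the scale. The HADS depression score is the natural reading: it is the primary outcome and the baseline covariate, and the only other depression measure in the table, the PHQ-9, is listed with a single item. I assume whole-number HADS-D scores from 0 to 21. The article does not state this range, but its cut-offs are all whole numbers.

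**2. Coverage of the printed groups.**

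| Baseline score | < 10 | ≥11 | Group |
|---|---|---|---|
| 0 to 9 | yes | no | lower |
| 10 | no | no | none |
| 11 to 21 | no | yes | upper |

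Exactly one score, 10, is unassigned. With ≤10 versus ≥11, none is.

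**3. Whether such patients can be in the trial.** A depression score of 10 is above the entry limit of 8, and it still counts as positive at the baseline check. They can be.

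**4. Denominators.** The Sample size calculation section takes "standard deviation of the mean of the HADS depression score at 3 months is 3.5" and "The minimal clinically important difference for the HADS is 2 points", with 90% power and 5% type 1 error, and states 66 per group, 94 after 30% dropout and 188 in total. Check, two-sided:

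- n = 2 × (1.960 + 1.282)² × 3.5² / 2² = 64.4, so 65 per group by the normal formula.
- The t-test version gives 66 (power 0.899 at 65 and 0.903 at 66), which matches the stated figure.
- 66 / 0.70 = 94.3. The article states 94; strict rounding up would give 95, which is immaterial here.

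The planned evaluable number is 2 × 66 = 132, and the planned randomised number is 188.

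**5. How many patients might score 10.** The article gives no baseline mean or SD; its only SD, 3.5, is for the 3-month score. I therefore assume a normal distribution with mean m and SD s, rounded to whole scores and rescaled to sum to 1 over 0 to 21:

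P(10) ∝ Φ((10.5 − m)/s) − Φ((9.5 − m)/s)

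Worked case, m = 8 and s = 3.5: Φ(0.714) − Φ(0.429) = 0.097, so 18.3 of 188 and 12.8 of 132.

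| Mean | SD 3 | SD 3.5 | SD 4 |
|---|---|---|---|
| 6 | 5.6% | 6.1% | 6.4% |
| 7 | 8.1% | 8.0% | 7.8% |
| 8 | 10.6% | 9.7% | 8.9% |
| 9 | 12.5% | 10.9% | 9.7% |
| 10 | 13.2% | 11.4% | 10.0% |

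The range is 5.6% to 13.2%. That is 7.4 to 17.5 of 132 evaluable patients, or 10.5 to 24.9 of 188 randomised. The lower means are included because patients can enter on anxiety alone, which would pull the average depression score down.

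**The case against.** The strongest reply is that this is a slip whose intent can be recovered. The article gives ≥11 twice, the second time with its meaning, so the upper group is fixed and its complement is ≤10. That stands, and it is why the fix is obvious. It does not make the printed rule correct: an analyst who follows it literally still omits these patients.

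The reply also says that little depends on this line. That stands too. The primary regression and the longitudinal mixed model do not use the cut, three of the four subgroup analyses are untouched, and the sample size rests on the overall comparison only.

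A reader might be tempted to go further in three ways that the article does not support.

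- **That an interaction estimate is affected.** The article names no interaction term or estimation method for the subgroups. It says only that subgroup analyses will be done, and the method may be in an analysis plan that is not shown.
- **That score-10 patients could be placed in whichever group suits.** With ≥11 fixed as the upper group, nothing in the text supports placing them there. The real ambiguity is between including them in the lower group and omitting them.
- **That splitting scores is itself an error, so that "age (median split" is a second instance.** The median split sets a rule on a pre-randomisation variable and leaves no gap. Preferring continuous interactions is a choice of method that brings its own linearity assumption. It does not correct anything the article states wrongly.

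**Conclusion.** The definition is wrong as written: patients with a baseline score of exactly 10 are eligible and belong to neither subgroup. The consequence is confined to one of four pre-planned subgroup analyses, and the severity is minor. It would be wrong to infer any effect on the primary result, because these patients stay in the primary analysis.

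The existence of the gap rests only on whole-number scoring. Its size, about 6% to 13% of patients or roughly 7 to 18 of 132 evaluable, rests on an assumed baseline distribution and should be read as an illustration. If scores prorated for missing items were allowed, values between 10 and 11 would also be unassigned.

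**What to change.** In Statistical methods, change subgroup (iv) to baseline HADS-D ≤10 versus ≥11, naming the scale, and carry the same wording into the analysis plan. This keeps the article's moderate threshold and makes the groups exhaustive. If the full protocol allows prorated scores, write the lower group as < 11, which is identical on whole numbers and leaves no gap between them.

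The cost is one line, with no change to the sample size, the primary analysis or data collection. The Trial status section reports 31 of 188 patients included on 17 December 2020, so at that date the correction could still have been recorded well before the 3-month data were complete. In any case it should be made and dated before outcomes are examined by group.

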## Trial status

The first patient was included into the trial on 22 May 2020. Now (17 December 2020) we have 31 patients included into the trial of the 188 patients required.

## Discussion

The multi-disciplinary *eMindYourHeart* trial is highly relevant due to projections that IHD and depression will be among the top contributors to the disease-burden worldwide in 2020 [2, 11, 12]. CR programs show mixed efficacy with respect to targeting vulnerable patients who are at risk of refusing or dropping out of the program [17]. There is an absence of treatment for patients who screen positive for depression and anxiety, as screening for depression and anxiety in patients with IHD combined with treatment are far from universally implemented [20]. If proven effective, *eMindYourHeart* holds a strong potential for improving the quality of care of the increasing population of patients with IHD and comorbid depression and anxiety, with likely benefits to patients, families, the healthcare system and society at large due to potential reductions in direct and indirect costs. The trial evaluates both the efficacy and the cost-effectiveness of the intervention, which is adherent to the recommendations by the American Heart Association [43] and the European Society of Cardiology [44].

## Limitations

We are not able to blind patients to their condition, which may lead to bias and exaggeration of the effect [45]. The results may not be generalisable to the population of patients with IHD and comorbid depression and anxiety, as we cannot include patients who are not referred for CR or who refuse participation. Only patients who are able to use a computer and log into the platform are eligible. Some patients (e.g. depressed patients) may not have the motivation and energy to participate, which may lead to a potential selection bias.

## Conclusions

*eMindYourHeart* will provide new insights into the efficacy and acceptance of a therapist-assisted internet treatment for patients with IHD and comorbid depression and anxiety as part of standard CR that was designed with and for this patient group. This may increase the application’s quality and level of user acceptance [46, 47].

## Data Availability

Datasets from the study will be made available upon request to the corresponding author once the trial has been completed and all papers in the *eMindYourHeart* publication charter have been published.

## Abbreviations

AMI: Acute myocardial infarction
CONSORT: Consolidated standards of reporting trials
CR: Cardiac rehabilitation
DHRD: Danish cardiac rehabilitation database
DSMB: Data safety monitoring board
GDPR: General data protection regulation directive
GP: General practitioner
HADS: Hospital anxiety and depression scale
ICD: Implantable cardioverter defibrillator
IHD: Ischaemic heart disease
OPEN: Open patient data explorative network
RCT: Randomised controlled trial
REDCap: Research electronic data capture
SCAN: Schedules for clinical assessment in neuropsychiatry
SD: Standard deviation
TAU: Treatment as usual
QoL: Quality of life
